## 2.5 Description of the acts and procedures added by the research

The start of the study evaluation periods (i.e. control strategy period and intervention strategy period during which SARS-CoV-2 screening will be offered by nurses) will be randomly assigned for each site following a “cluster and crossover per period” randomisation.

During the intervention strategy period, the proposal of a self-administered questionnaire will be the other procedure added by the research (see addendum 2). The questionnaire concerns SARS-CoV-2 symptoms, contagion possibilities and situations at risk of exposure, as well as sociodemographic characteristics. It was developed by the research team from other questionnaires currently used in France (SocialCov and ComCor questionnaires, Pasteur Institute) or elsewhere .

Regardless of the answers to the questionnaire, SARS-CoV-2 screening by nasopharyngeal sampling will be offered by the triage nurse (*infirmier organisateur de l'accueil*, IOA) or the nurse in the cubicle.

A multiplex PCR test for symptomatic patients or an RT-LAMP test for asymptomatic patients will be performed, according to the symptomatology reported in the self-questionnaire.

During this period, the doctor may also offer a test to the patient if he/she has not already been offered by the nurse.

After performing a test, the patient will be treated according to the circuit defined in each hospital.

In the event of a positive test, if the patient is hospitalised, his/her care will be carried out according to the circuit defined by each hospital. Non-hospitalised patients will be referred to COVISAN or the usual department for follow-up and contact tracing. In the event of a negative test, the usual emergency procedure will follow.

For patients with a positive SARS-CoV-2 test and who have not completed the DEPIST-COVID self-administered questionnaire, a subsequent telephone follow-up will be performed to retrieve their profile based on the questions in the self-administered questionnaire. Patients will be accompanied by the research staff to complete the ComCor questionnaire of the Pasteur Institute to facilitate the study of sociodemographic, behavioural factors and practices associated with SARS-CoV-2 infection.

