### 6.3.3 Intervention strategy

- A self-administered questionnaire (see addendum 2) on SARS-CoV-2 symptoms, contagion possibilities, situations at risk of exposure as well as socio-demographic characteristics will be offered to enrolled patients who are able to complete it. It was developed by the research team from other questionnaires currently used in France (SocialCov and ComCor questionnaires, Pasteur Institute) or elsewhere .
- The patient will fill out the questionnaire and submit it directly to the triage nurse (IOA), or the attending nurse at the time of care. If necessary, the nurse will complete the questionnaire with the patient.
- In the triage room or in a cubicle, SARS-CoV-2 screening will be offered by the nurse regardless of the answer to the questionnaire. According to the decree of 24/07/2020, nurses are authorised to perform, without medical prescription, nasopharyngeal sampling procedures for SARS-CoV-2 infection testing; trained caregivers are also authorised to do so under the responsibility of a physician or a qualified nurse from their institution.
- A nasopharyngeal sample for SARS-CoV-2 test will be taken in a cubicle by the nurse in compliance with the performance conditions and in particular the personal protection measures recommended in the hospital protocol, with the exception of patients who cannot have a nasopharyngeal sample (thrombocytopenia, ENT malformation). In case of contraindication to nasopharyngeal sampling, oropharyngeal sampling is indicated, according to the HAS recommendations . The choice of test will be determined based on the presence of suggestive symptoms.
- The patient will note agreement to participate in the study on page 1.
- A patient with one or more symptoms listed in the patient questionnaire will be considered symptomatic.
- A multiplex PCR test will be performed for patients with symptoms suggestive of SARS-CoV-2 infection, known as “symptomatic”, on medical advice. The analysis time is 75 minutes.
- For patients with no symptoms suggestive of SARS-CoV-2 infection, known as “asymptomatic”, an RT-LAMP test will be performed. The analysis time is 5 to 15 minutes.

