In addition and if possible within the timeframe imposed by the project, the flow data by severity and time of patient visit (including: date and time of entry, month and year of birth, sex, reason for visit given to the triage nurse or IOA, diagnosis at discharge and severity (in order to count patients who are eligible for the self-questionnaire), date and time of discharge) will be collected via an extraction from the clinical activity database used by the sites (URQUAL, ORBIS, SUMD, for example) and which will be anonymised. If necessary, data extraction will be the subject of a request to the dedicated committees (request for authorisation from the scientific and ethics committee of the health data warehouse for the AP-HP services, for example).

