##### Secondary endpoints analyses

- The proportion of patients tested positive for SARS-CoV-2 among the asymptomatic or paucisymptomatic patients tested by nurses and that in the Paris Metropolitan area at the same period will be compared using an asymptotic Wald test.  
The proportion obtained in each emergency department will be compared to that of the department's IRIS geographical area using an asymptotic Wald test. The same comparisons will be made across the entire tested population.
- The feasibility of the testing will be described: proportion of patients who have completed the questionnaire, proportion of offered, accepted and performed tests, and notified of the SARS-CoV-2 result and staff involved (nurses, caregivers, doctors, others),
- The proportion of patients tested positive for SARS-CoV-2 among the patients tested by nurses, the proportion of asymptomatic patients among the patients tested by nurses and the proportion of asymptomatic patients among the patients tested positive for SARS-CoV-2 will be described.

|                        |              |
|------------------------|--------------|
| Study                  | DEPIST-COVID |
| Promotion/gestion code | APHP201625   |
| Study coordinator      | [name]   |

- The symptoms of patients tested positive for SARS-CoV-2 will be described in the patients completed the questionnaire.
- Exposure factors will be described using the items in the DEPIST-COVID questionnaire. Among patients tested, the exposure factors associated with the positivity of the SARS-CoV-2 test will be analysed using a generalised linear mixed model (binomial distribution or other distribution adapted to the data). The exposure factors will be considered as fixed effects and the site as a random intercept. Other fixed variables could be added to the model if appropriate.
- The sociodemographic, behavioural and practical factors of diagnosed patients associated with positive SARS-CoV-2 infection will be described for the schemes (DEPIST-COVID, ComCor) according to the types of variables (proportion, mean and standard deviation or median, Q1-Q3) and presented with their 95% confidence interval. If appropriate, the factors will also be analysed in the population of DEPIST-COVID cases (positive tested patients) and controls (negative and matched tested patients).

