### **Secondary endpoints analyses**

- Factors associated with performing systematic nurse-driven screening will be analysed in patients who had screening offer using a generalised linear mixed model (binomial distribution) with the centre as a random intercept and the patient characteristics as fixed effects.

- The factors associated with new SARS-CoV-2 diagnoses will be analysed using a generalised linear mixed model (binomial distribution) with the centre as a random intercept and patient characteristics as fixed effects.

- The proportions of new SARS-CoV-2 diagnoses through systematic nurse-driven screening overall and per ED, and proportion among all patients tested in EDs, will be compared to the proportion of positive tests among adults tested in the geographical departments of the Paris Metropolitan area using the Miettinen-Nurminen method for risk difference and 95% CI estimations.

[figure not shown]

Coller ici l'étiquette patient

N° DOSSIER :

\_\_\_\_\_  
Centre

\_\_\_\_\_  
Patient

PLEASE FILL OUT THIS QUESTIONNAIRE BY CHECKING THE SQUARE  
CORRESPONDING TO YOUR RESPONSE [figure not shown]

1 You are:

☐ male ☐ female

2 What is your date of birth?

Month Year

3 Do you have symptoms suggestive of Covid-19?

☐ Yes ☐ No

> If yes, please precise:

☐ Fever (>38°C)  
or fever sensation

☐ Cough

☐ Loss of smell

☐ Muscular pain

☐ Unusual fatigue

☐ Breathing difficulty  
(shortness of breath)

☐ Loss of taste

☐ Other

☐ Headache

☐ Sore throat

☐ Diarrhoea

☐ Runny nose

> If yes, date of first symptoms:

Day Month Year

4 What is your postcode?

5 In which country were you born?

☐ France

☐ Other

Please specify your country of birth:

6 Until what age did you study?

years

7 Currently (over the last month):

☐ You work

☐ You do not work

☐ You are seeking employment

☐ You are a student

> If you work:

• Do you work away from home?:

☐ Yes

☐ No

☐ Partially

• Does your occupation expose you to contacts with:

- Members of the public?

☐ Yes

☐ No

- Sick persons?

☐ Yes

☐ No

8 What is your medical coverage:

☐ Social security without supplementary health insurance

☐ CMU (Universal medical cover)

☐ Social security with supplementary health insurance

☐ AME (State medical assistance)

☐ No medical coverage

☐ Other

9 Do you suffer from a chronic disease (diabetes, high blood pressure, angina pectoris, chronic bronchitis, asthma or chronic respiratory disease)?

☐ Yes

☐ No

10 Do you currently smoke cigarettes?

☐ Yes

☐ No

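### Question 3 shows the symptom list only to patients who first say their symptoms suggest Covid-19, so the protocol's listed-symptom rule cannot be applied to those who answer No, and the two asymptomatic shares can only be too high or unchanged

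*Combined protocol and SAP*

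**What the plan says.** Protocol section 6.3.3 (Intervention strategy) gives a list-based rule: "A patient with one or more symptoms listed in the patient questionnaire will be considered symptomatic". The same section also describes the asymptomatic group by a judgement rather than by a list: "For patients with no symptoms suggestive of SARS-CoV-2 infection, known as “asymptomatic”, an RT-LAMP test will be performed". The two wordings are not reconciled.

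Section 2.5 says the classification comes from the form, with the test chosen "according to the symptomatology reported in the self-questionnaire". Staff can be involved: "If necessary, the nurse will complete the questionnaire with the patient". Section 6.3.3 also makes the multiplex test subject to medical advice.

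Question 3 of the DEPIST-COVID questionnaire asks "Do you have symptoms suggestive of Covid-19", to be answered Yes or No. The twelve symptom boxes (eleven named symptoms and an Other box) follow under "If yes, please precise".

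SAP 1.1 (Secondary endpoints analyses) plans to describe "the proportion of asymptomatic patients among the patients tested by nurses and the proportion of asymptomatic patients among the patients tested positive for SARS-CoV-2".

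**The concern.** The definition and the form do not match. The definition asks whether a listed symptom is present. The form asks whether the patient thinks his or her symptoms point to Covid-19, and goes to the list only if so. Headache, fatigue, diarrhoea, muscle pain and breathlessness are common reasons to attend an emergency department. A patient who puts one of them down to another cause can truthfully answer No, yet would be symptomatic under the section 6.3.3 rule.

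Finding infected people without symptoms is a main reason for the trial. The share of asymptomatic patients among those tested, and among those found positive, is therefore a figure that readers will look for. Under the listed-symptom rule, the gate can move patients in one direction only, from symptomatic to asymptomatic.

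**Working it through.** **Inputs.** All come from Table E1 and its footnotes (patients tested through nurse screening, excluding indeterminate results and known positives):

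- Symptoms Yes: 766 of 4,062 overall, 133 of 216 new diagnoses, 633 of 3,846 negatives.
- Denominators of the twelve symptom rows: 754 to 760.
- Reported symptoms by test: 258 (7.4%) of RT-LAMP patients and 508 (90.1%) of multiplex patients.
- Symptom answer missing: 4,192 − 4,062 = 130 patients, of whom 224 − 216 = 8 were positive.

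**Step 1. Reproduce the printed figures.** 766/4,062 = 18.9%; 133/216 = 61.6%; 633/3,846 = 16.5%. All match the table.

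**Step 2. Check the skip.** Every symptom row has a denominator just below 766, the number who said Yes. That is what the gate would produce. No listed symptom is reported for the remaining 4,062 − 766 = 3,296 patients.

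**Step 3. The asymptomatic group as recorded.**

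- Among tested: 3,296/4,062 = 81.1%.
- Among positives: (216 − 133)/216 = 83/216 = 38.4%.
- Positivity: No group 83/3,296 = 2.5%; Yes group 133/766 = 17.4%.

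**Step 4. Direction and possible size.** Let m be the share of the No group who had a listed symptom, and q the positivity of those patients. The documents give neither. Then:

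- share among tested = 3,296(1 − m)/4,062;
- share among positives = (83 − 3,296·m·q)/216;
- positivity of the remaining asymptomatic group = (83 − 3,296·m·q)/[3,296(1 − m)].

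The first two can only fall or stay the same as m rises. The third falls only if q exceeds 83/3,296 = 2.5%.

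The range assumed for q runs from the No-group rate to the Yes-group rate:

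| m (assumed) | q (assumed) | Misclassified positives | Share among tested | Share among positives | Positivity, remaining group |
|---|---|---|---|---|---|
| 0 | – | 0 | 81.1% | 38.4% | 2.5% |
| 5% | 2.5% | 4.2 | 77.1% | 36.5% | 2.5% |
| 5% | 17.4% | 28.6 | 77.1% | 25.2% | 1.7% |
| 10% | 2.5% | 8.3 | 73.0% | 34.6% | 2.5% |
| 10% | 17.4% | 57.2 | 73.0% | 11.9% | 0.9% |

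**Step 5. Agreement between answer and test.** Multiplex patients with an answer: 508/0.901 ≈ 564, so about 564 − 508 = 56 of them answered No. RT-LAMP patients with an answer: 4,062 − 564 = 3,498, and 258/3,498 = 7.4%, which agrees with the footnote. The answer and the test therefore disagree in both directions: about 56 No patients had multiplex and 258 Yes patients had RT-LAMP. Moving the 56 out of the asymptomatic group gives 3,240/4,062 = 79.8% of those tested. The effect on the share among positives cannot be computed, because the table does not give the number of positives among the 56.

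**Step 6. What does not depend on question 3.** The primary outcome counts new diagnoses over all consulting adults. The regional comparison in SAP 1.1 pools asymptomatic and paucisymptomatic patients, and Table J1 uses all nurse-screened patients (224/4,283 = 5.2% against 156,298/3,400,584 = 4.6%). Neither changes.

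**The case against.** The best defence is that section 6.3.3 also describes the asymptomatic group as patients without suggestive symptoms, and question 3 measures that directly. Under this wording nothing is misclassified; the measure is merely subjective. This stands, and it is why the overstatement is conditional on the listed-symptom rule. It also means that the protocol holds two definitions and the form serves only one.

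Second, this is a paper form with the list printed under the question, and a nurse may help to complete it. The row denominators would also arise if the table had simply been restricted to Yes answers. All true, so Table E1 fits the skip without proving it. But the nurse works with the same form, and no passage asks staff to go through the list after a No.

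Third, a reader might infer that positivity among asymptomatic patients is inflated. The documents do not support that. It requires the misclassified patients to have above-average positivity, which is not observed. Among Yes patients, headache (38.6% of positives against 42.7% of negatives), diarrhoea (9.1% against 14.5%) and breathlessness (27.8% against 28.2%) were no more common in positives.

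Fourth, a reader might take the roughly 56 No patients given multiplex as proof of hidden symptoms. The 258 Yes patients given RT-LAMP show that test choice did not simply follow the answer, and no reason is given for either mismatch.

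Finally, the results tables already use a combined asymptomatic/paucisymptomatic label. That helps the regional comparison, but the two shares in SAP 1.1 still use asymptomatic alone.

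**Conclusion.** The point holds for two descriptive secondary endpoints: the asymptomatic share among patients tested by nurses (81.1% as recorded) and among positives (38.4%). Under the listed-symptom rule, both can only be too high or unchanged. The amount is unknown, because no listed-symptom data are reported for the 3,296 No patients. With m of 5% to 10% and q of 2.5% to 17.4%, all assumed, the share among tested would be 77.1% to 73.0%, and the share among positives between about 36.5% and 12%.

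A reader might go further and conclude that the asymptomatic results as a whole are shown to be overstated, or that the trial's main comparison is biased. Neither follows. The first turns a possible direction under one of two definitions into an established fact. The second fails because neither the primary outcome nor the regional comparison uses question 3.

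**What to change.** **Form, for any further use.** Have every patient tick each listed symptom or none. Keep the Covid-suggestive question as a separate item. Derive symptomatic status for the endpoints from the list. Reconcile the two wordings in section 6.3.3. This concerns the endpoint variable only; which test a patient receives is for the protocol's authors to settle. They should note that an ungated list with headache, fatigue and Other could class many more patients as symptomatic. If test choice followed it, the planned daily mix in section 13.1 (19 RT-LAMP and 12 multiplex per site) could shift.

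**Data already collected.** In SAP 1.1, report the group as having 'no self-declared Covid-suggestive symptoms'. Add a sensitivity analysis that reclassifies the roughly 56 No patients who received multiplex (question 27 of the form), and report the 258 RT-LAMP patients who declared symptoms beside it. Section 12.1 also foresees extracting "reason for visit given to the triage nurse or IOA, diagnosis at discharge and severity". That extraction is conditional on time, anonymised, and not described as linked to the questionnaires, so use it only if patient-level linkage proves possible.

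**Cost.** Slightly longer form completion, a change of label, one extra analysis, and a possibly lower asymptomatic share.

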## OVER THE LAST 10 DAYS:

14 Apart from at home, have you always worn a mask? ☐ Yes ☐ No

---

15 Have you always worn a mask with friends or family that you do not live with? ☐ Yes ☐ No

---

16 Have you always kept within at least one meter in the following situations?

- At work or school: ☐ Yes ☐ No
- With friends or family: ☐ Yes ☐ No

---

17 Have you been in close contact with someone who has tested positive for Covid-19?

☐ Yes, 1-2 times ☐ Yes, 3 times or more ☐ No

> If yes, please precise:

☐ Family who you live with ☐ Family who you do not live with ☐ Friend

☐ Colleague ☐ Notification by the TousAntiCovid app ☐ Other

---

18 Have you been out of your home:

- For work? ☐ Yes, 1-2 times ☐ Yes, 3 times or more ☐ No
- For your studies? ☐ Yes, 1-2 times ☐ Yes, 3 times or more ☐ No

---

19 Have you used public transport? ☐ Yes, 1-2 times ☐ Yes, 3 times or more ☐ No

---

20 Have you been to a restaurant or a bar? ☐ Yes, 1-2 times ☐ Yes, 3 times or more ☐ No

---

21 Have you been to a gym/sports hall? ☐ Yes, 1-2 times ☐ Yes, 3 times or more ☐ No

---

22 Have you been to a gathering of more than 5 people?

☐ Yes, 1-2 times ☐ Yes, 3 times or more ☐ No

> If yes, for the busiest gathering:

- What type of gathering was it?

☐ For work ☐ At school/university ☐ A cultural site (cinema, theatre)

☐ A religious gathering ☐ A private gathering (friends/family) ☐ Other

- Was the gathering in: ☐ a Closed space ☐ An open space ☐ Both
- How many people were there: ☐ 5-10 ☐ 10-20 ☐ 20-50 ☐ > 50 people
- Were you wearing a mask? ☐ Yes ☐ No

> If yes: did you wear the mask the whole time? ☐ Yes ☐ No

- Were you more than one meter away from every person? ☐ Yes ☐ No

---

23 Have you been hospitalised? ☐ Yes, 1-2 times ☐ Yes, 3 times or more ☐ No

---

24 Have you taken a Covid-19 screening test? ☐ Yes, 1-2 times ☐ Yes, 3 times or more ☐ No

> If yes:

- Was it a: ☐ Nasopharyngeal swab ☐ Blood test (serology) ☐ Saliva swab
- Was the test? ☐ Positive ☐ Negative

> If positive: what was the date of the last positive test?

Day Month Year

---

25 How would you evaluate your risk of getting infected with Covid-19 compared to other people?

Risk: ☐ Very high ☐ High ☐ Similar ☐ Low ☐ Very low

---

## PARTIE A REMPLIR PAR L'INFIRMIER(E)

Le patient accepte de participer à l'étude et de réaliser un test :

☐ Oui

☐ Non

26 Test réalisé :

☐ Oui

☐ Non

27 Type de test :

☐ RT-LAMP

☐ PCR multiplex

### SI TEST NON RÉALISÉ

28 Motifs (Plusieurs choix possibles) :

☐ Refus :

☐ Déclare un test récent :

date :

Mois Année

☐ Déclare ne pas avoir de risque

☐ Patient vacciné contre la Covid-19

☐ Autre refus

☐ Consultant dans l'impossibilité de donner un accord

☐ Consultant parti

☐ Impossibilité liée au service

Commentaires :

Nom de l'infirmier(e) :

### SI TEST RÉALISÉ

29 Heure de lancement du test :   h

30 Heure de lecture du test :   h

31 Résultat du test SARS-CoV2 :

☐ Négatif

☐ Positif

☐ Ininterprétable

> Refaire le test : ☐ Négatif

☐ Positif

☐ Ininterprétable

32 Autres virus respiratoires (si applicable) :

☐ Négatif

☐ Positif

> Précisez le virus

33 Rendu du résultat au consultant :

☐ Oui ☐ Non

> Si non : motif :

34 Informations complémentaires :

Test proposé par :

☐ Infirmier(e) ☐ Aide-soignant(e) ☐ Médecin

☐ Equipe de recherche

Test réalisé par :

☐ Infirmier(e) ☐ Aide-soignant(e) ☐ Médecin

☐ Equipe de recherche

## POUR LE PERSONNEL DE RECHERCHE

ÉTUDE ANCILLAIRE :

☐ Oui ☐ Non

Test Antigénique :

☐ Oui ☐ Non

Résultat : ☐ Positif ☐ Négatif ☐ Ininterprétable

Milieu de transport :

☐ Oui ☐ Non

Résultat : ☐ Positif ☐ Négatif ☐ Ininterprétable

Si nécessaire, indiquer le numéro du questionnaire Depist Covid du patient témoin :

DEVENIR DU PATIENT :

☐ Ambulatoire

☐ Hospitalisé

☐ Soins intensifs

Appendix B. Figure Geographical location of the 18 emergency departments involved in the DEPIST-COVID trial (Paris metropolitan area)

Fig B1. Geographical location of the 18 emergency departments involved in the DEPIST-COVID trial (Paris metropolitan area)

[figure not shown]

*References:*

R Core Team (2022). *R: A language and environment for statistical computing*. R Foundation for Statistical Computing, Vienna, Austria. URL <https://www.R-project.org/>.  
Hijmans, R.J. (2022). *raster: Geographic Data Analysis and Modeling*. R package version 4.1.3. <https://CRAN.R-project.org/package=raster>.

# Appendix C. Table Emergency department characteristics and study period duration

Table C1. Emergency department characteristics and study period duration

| ED center                                                     | 1     | 2     | 3     | 4     | 5     | 6     | 7     | 8     | 9     | 10    | 11    | 12    | 13    | 14    | 15    | 16    | 17    | 18    |
|---------------------------------------------------------------|-------|-------|-------|-------|-------|-------|-------|-------|-------|-------|-------|-------|-------|-------|-------|-------|-------|-------|
| Pediatric care                                                | 0     | 0     | 0     | 0     | 1     | 0     | 1     | 0     | 1     | 0     | 1     | 1     | 0     | 0     | 0     | 1     | 0     | 0     |
| University hospital                                           | 1     | 1     | 1     | 1     | 0     | 1     | 1     | 1     | 0     | 1     | 1     | 1     | 1     | 1     | 0     | 1     | 0     | 1     |
| Inner Paris ED                                                | 1     | 1     | 1     | 0     | 0     | 0     | 0     | 1     | 0     | 0     | 0     | 0     | 1     | 1     | 0     | 0     | 1     | 1     |
| Annual patient admissions in 2021 a                | 74654 | 50891 | 57430 | 43990 | 91752 | 39977 | 96287 | 76855 | 53692 | 33083 | 59663 | 68957 | 58560 | 34630 | 26183 | 57635 | 62700 | 47550 |
| SARS-CoV-2 device for rapid testing in routine care in the ED | 1     | 1     | 1     | 1     | 0     | 1     | 0     | 1     | 0     | 0     | 0     | 0     | 1     | 1     | 0     | 0     | 1     | 0     |
| Control study period (days) b                      | 37    | 33    | 26    | 34    | 35    | 35    | 36    | 29    | 40    | 30    | 32    | 30    | 31    | 40    | 40    | 35    | 35    | 25    |
| Intervention study period (days) b                 | 37    | 33    | 26    | 34    | 35    | 35    | 36    | 29    | 38    | 30    | 32    | 30    | 31    | 40    | 40    | 35    | 35    | 30    |
| Wash-out study period (days) b                     | 1     | 2     | 1     | 1     | 2     | 1     | 2     | 1     | 2     | 1     | 2     | 1     | 2     | 1     | 1     | 2     | 7     | 2     |

Data are presented as numbers or No 0/Yes 1.

ED: Emergency department.

aAnnual patient admissions included pediatric admissions.

bDuration of the intervention, control, and wash-out periods (days), median [first quartile, third quartile]: 34.5 [30.0, 36.0]; 34.5 [30.0, 36.0]; 1.5 [1.0, 2.0].

Appendix D. Table Characteristics of patients who underwent and declined SARS-CoV-2 screening for asymptomatic/paucisymptomatic patients during the intervention period

Table D1. Characteristics of patients who underwent and declined SARS-CoV-2 screening for asymptomatic/paucisymptomatic patients during the intervention period

|                                                                              | Total population
N=5 841* |                                | SARS-CoV-2 screening
for asymptomatic /
paucisymptomatic
patients performed
n=4 283 |                                | SARS-CoV-2 screening for
asymptomatic /
paucisymptomatic
patients declined
n=1 558 |                             | Risk difference            |
|------------------------------------------------------------------------------|------------------------------|--------------------------------|-------------------------------------------------------------------------------------------------|--------------------------------|------------------------------------------------------------------------------------------------|-----------------------------|----------------------------|
|                                                                              | N                            | n (%)
or median [Q1,
Q3] | N                                                                                               | n (%)
or median [Q1,
Q3] | N                                                                                              | n (%)
or median [Q1, Q3] | %
or median (95%
CI) |
| Age (years)                                                           | 5771                         | 40.0 [28.0, 55.0]              | 4257                                                                                            | 41.0 [29.0, 56.0]              | 1514                                                                                           | 37.0 [27.0, 54.0]           | 4.0 (2.6, 5.4)             |
| Sex                                                                   | 5831                         |                                | 4278                                                                                            |                                | 1553                                                                                           |                             |                            |
| Female                                                                       |                              | 2696 (46.2)                    |                                                                                                 | 1942 (45.4)                    |                                                                                                | 754 (48.6)                  | -3.2 (-6.1, -0.3)          |
| SARS-CoV-2 symptoms                                                   | 5610                         |                                | 4148                                                                                            |                                | 1462                                                                                           |                             |                            |
| Yes                                                                          |                              | 888 (15.8)                     |                                                                                                 | 794 (19.1)                     |                                                                                                | 94 (6.4)                    | 12.7 (10.9, 14.4)          |
| Symptom delay (days)                                                  | 578                          | 3.0 [1.0, 7.0]                 | 530                                                                                             | 3.0 [1.0, 7.0]                 | 48                                                                                             | 4.0 [2.5, 11.0]             | -1.0 (-3.4, 1.4)           |
| Country of birth                                                      | 5214                         |                                | 3945                                                                                            |                                | 1269                                                                                           |                             |                            |
| France                                                                       |                              | 3130 (60.0)                    |                                                                                                 | 2338 (59.3)                    |                                                                                                | 792 (62.4)                  | -3.1 (-6.2, -0.05)         |
| Other                                                                        |                              | 2084 (40.0)                    |                                                                                                 | 1607 (40.7)                    |                                                                                                | 477 (37.6)                  | 3.1 (0.05, 6.2)            |
| Region of birth                                                       | 1853                         |                                | 1440                                                                                            |                                | 413                                                                                            |                             |                            |
| Europe (outside France)                                                      |                              | 268 (14.5)                     |                                                                                                 | 211 (14.7)                     |                                                                                                | 57 (13.8)                   | 0.9 (-3.2, 4.4)            |
| Americas outside the Caribbean                                               |                              | 87 (4.7)                       |                                                                                                 | 74 (5.1)                       |                                                                                                | 13 (3.1)                    | 2.0 (-0.4, 3.8)            |
| Asia-Middle East                                                             |                              | 224 (12.1)                     |                                                                                                 | 180 (12.5)                     |                                                                                                | 44 (10.7)                   | 1.8 (-1.9, 5.1)            |
| France overseas and Caribbean                                                |                              | 63 (3.4)                       |                                                                                                 | 48 (3.3)                       |                                                                                                | 15 (3.6)                    | -0.3 (-2.7, 1.5)           |
| Sub-Saharan Africa                                                           |                              | 474 (25.6)                     |                                                                                                 | 369 (25.6)                     |                                                                                                | 105 (25.4)                  | 0.2 (-4.7, 4.8)            |
| North Africa                                                                 |                              | 729 (39.3)                     |                                                                                                 | 551 (38.3)                     |                                                                                                | 178 (43.1)                  | -4.8 (-10.3, 0.5)          |
| Oceania                                                                      |                              | 5 (0.3)                        |                                                                                                 | 5 (0.3)                        |                                                                                                | 0 (0)                       | 0.3 (-0.6, 0.8)            |
| Until what age did you study? (year)                                  | 4528                         | 20.0 [18.0, 24.0]              | 3431                                                                                            | 20.0 [18.0, 24.0]              | 1097                                                                                           | 20.0 [18.0, 24.0]           | 0.0 (-0.3, 0.3)            |
| Currently (within last month)                                         | 5202                         |                                | 3925                                                                                            |                                | 1277                                                                                           |                             |                            |
| You work                                                                     |                              | 3034 (58.3)                    |                                                                                                 | 2268 (57.8)                    |                                                                                                | 766 (60.0)                  | -2.2 (-5.3, 0.9)           |
| You do not work                                                              |                              | 1414 (27.2)                    |                                                                                                 | 1115 (28.4)                    |                                                                                                | 299 (23.4)                  | 5.0 (2.2, 7.7)             |
| You are searching for a job                                                  |                              | 368 (7.1)                      |                                                                                                 | 257 (6.5)                      |                                                                                                | 111 (8.7)                   | -2.1 (-4.0, -0.5)          |
| You are a student                                                            |                              | 321 (6.2)                      |                                                                                                 | 233 (5.9)                      |                                                                                                | 88 (6.9)                    | -1.0 (-2.6, 0.5)           |
| You are a student and you work                                               |                              | 65 (1.2)                       |                                                                                                 | 52 (1.3)                       |                                                                                                | 13 (1.0)                    | 0.3 (-0.5, 0.9)            |
| Do you work outside your home?                                        | 2949                         |                                | 2207                                                                                            |                                | 742                                                                                            |                             |                            |
| Yes                                                                          |                              | 2226 (75.5)                    |                                                                                                 | 1663 (75.4)                    |                                                                                                | 563 (75.9)                  | -0.5 (-4.0, 3.1)           |
